### Statistical methods

The statistical analysis will be performed by the Statistica package, version 13.0 (StatSoft, TIBCO Software Inc.). Before analysis, the Shapiro-Wilk test will be applied to examine the distribution of examined variables where normality will be assumed if p > 0.05. The chi-square test will be used to calculate differences in the qualitative data at baseline between groups. Depending on data distributions, the between-group comparisons will be performed using the ANOVA or Kruskal-Wallis rank-based nonparametric test for quantitative outcomes. To compare groups between baseline and endpoint assessments and follow-up assessments, repeated measures of ANOVA or aligned rank-transform ANOVA and McNemar’s test will be conducted. All analyses will be performed according to the ICH E9 Statistical Principles for Clinical Trials (67). Bonferroni correction of obtained significance levels will be used to correct for multiple comparisons. The additional characteristics of the participants and dropouts will be performed for an additional assessment of possible non-random differences.

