### Outcomes measures

#### Primary outcome measure

We hypothesize that the application of active tDCS will result in changes in the strength and variability of functional connectivity, with particular alterations in alpha (increase) and beta (decrease) frequencies, which will clinically lead to a reduction in the severity of psychopathological symptoms associated with AN, measured by the change in the EAT-26 scores between visit V1 (baseline) and V2 (end of stimulation after 3 weeks) as a primary outcome.

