#### Secondary outcome measures

For the purpose of evaluating the effectiveness of tDCS in treating AN, a range of secondary outcome measures will also be utilized, defined as changes in: 1. anthropometric measurements (in this BMI), 2. brain bioelectric activity, 3. nutritional status, 4. mood, 5. neurocognitive functions (attention, memory, and some aspects of planning, verbal fluency, and another executive function), 6. psychological measurements connected with: dysfunctional metacognitive beliefs, other aspects related to thinking such as reflectivity, impulsivity, rumination, obsessive-compulsive symptoms, stress levels and assessment of early childhood injuries related to the experience of abuse, emotional, bodily, sexual, emotional, and physical neglect, and self-assessment of the appearance of one’s body, 7. selected biological markers related to stress, food intake, inflammation and neurotrophins.

As regards the neurophysiological measures, we expect that a series of the tDCS sessions will be associated with changes in three aspects: 1. reduction of lower frequencies (delta and theta) in the dominant frequency spectrogram accompanied with an increase in the power of alpha and beta frequencies, 2. modification of alpha anterior asymmetry patterns associated with affective functioning towards less right-hemisphere-oriented and more left-hemisphere oriented pattern, 3. changes in the strength and variability of functional connectivity, with particular alterations regarding alpha (increase) and beta (decrease) frequencies, what is associated with the ability to gain more relaxed and less tensive states recorded during resting-state condition. The neurophysiological examination will be conducted during the V1 and V2 meetings.

Secondary psychological outcome measures will be gathered during the initial assessment (V1) and V2, while nutritional data will be collected at V1, V2, and V3 after follow-up. Biological outcomes will be recorded at V1 and V2, with additional measurements of BMI and BIA analysis also at V3. Neurophysiological outcome measures will be obtained during V1 and V2.

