### Study timeline

This study will consist of four visits:

V0: Screening visit to screen and enroll eligible patients into the study (1 to 2 days before the baseline visit).V1: Baseline visit 1 day (before intervention) to randomize patients, conduct assessments using questionnaires, perform a body composition analysis, take blood samples and perform an EEG test;V2: Visit 2, up to 3 days after the end of the intervention period, after three weeks ( ± 1 days) from baseline;V3: End of Study Visit to complete all procedures in this study, after 5 weeks ( ± 7 days) from baseline visit.

The total duration from the screening to the end of the study will be 6 weeks at maximum.

Psychological assessments: 1. Beck Depression Inventory (BDI), 2. The Children’s Depression Inventory 2 (CDI 2), 3. The Meta-Cognitions Questionnaire (MCQ-A), 4. Perceived Stress Scale (PSS-10), 5. Childhood Trauma Questionnaire (CTQ), 6. The Attention and Perceptiveness Tests version 6/9, 7. The Rey-Osterrieth complex figure test (ROCF), 8. The Yale-Brown Obsessive Compulsive Scale (CY-BOCS), 9. Color connection test (CTT-1, CTT-2), 10. The Benton Visual Retention Test (BVRT),11. The Appearance Self-Rating Sheet (ASRS),12. The Ruminance-Reflectivity Questionnaire (RRQ), 13. The Verbal Fluency Test (VFT), 14. Matching Familiar Figures Test (MFF).

Neuropsychological assessment: EEG.

Dietary behaviors and nutrition assessments: 1. Eating Attitudes Test (EAT-26), 2. Questionnaire Eating Behaviors (QEB), 3. Food Intake Variety Questionnaire (FIVq), 4. Eating Disorder Examination Questionnaire (EDE-Q 6.0).

Biological assessments: 1. Complete blood count (CBC), 2. Ferritin, 3. TSH, 4. FT3, 5. FT4, 6. Phosphorus, 7.Magnesium, 8. Calcium, 9. Cortisol, 10. Neurotrophins, 11. Leptin, 12. Visfatin.

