### Sample size calculation

The number of studies that examined the effect of tDCS in patients with AN group is relatively small. To calculate the sample size, we analyzed the number of patients in the general population (patients suffering from AN in Poland) (65) and previous trials conducted by other authors (18), which reported improvement in EAT-26 scores. The statistical power was estimated at 80% to detect a difference in means of EAT-26. The baseline EAT-26 points was estimated at 72.7, with a 20-point improvement (18). To account for a dropout rate of 20%, a total of 50 individuals will be included to achieve a target number of 40 participants. Patients will be recruited for the study and randomized into two subgroups. The recruitment target was determined to ensure statistical power, which allows confirmation of the differences in the primary outcomes with an approximately 95% probability of correctly rejecting the null hypothesis. The calculation of sample size was performed using the STATISTICA software (StatSoft) and online sample size calculator (66).

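### No single test is tied to the primary EAT-26 endpoint and no option uses baseline as a covariate; one ANCOVA at V2 would settle both at no cost

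*Protocol article*

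**What the plan says.** The Primary outcome measure section fixes the endpoint: symptom reduction is "measured by the change in the EAT-26 scores between visit V1 (baseline) and V2 (end of stimulation after 3 weeks) as a primary outcome". The Sample size calculation section is framed on the same scale: "The statistical power was estimated at 80% to detect a difference in means of EAT-26".

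The Statistical methods section then describes two routes for quantitative outcomes.

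- Route 1, between groups: "Depending on data distributions, the between-group comparisons will be performed using the ANOVA or Kruskal-Wallis rank-based nonparametric test for quantitative outcomes". The choice rests on this rule: "the Shapiro-Wilk test will be applied to examine the distribution of examined variables where normality will be assumed if p > 0.05".
- Route 2, across visits: "To compare groups between baseline and endpoint assessments and follow-up assessments, repeated measures of ANOVA or aligned rank-transform ANOVA". The same sentence adds McNemar's test.

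On multiplicity the section says: "Bonferroni correction of obtained significance levels will be used to correct for multiple comparisons". It does not define the family of tests. It also commits to the ICH E9 principles.

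The Study timeline section places EAT-26 among the dietary and nutrition assessments. Table 1 marks that block at V1, V2 and V3, and the Secondary outcome measures section agrees: "while nutritional data will be collected at V1, V2, and V3 after follow-up". So EAT-26 scores will exist at V3, and route 2 can take them in.

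**The concern.** The time point of the primary endpoint is fixed, but the test is not. The two routes need not answer the same question. A comparison of V2 scores, a comparison of V1-to-V2 changes and a three-visit group-by-time test can disagree, and nothing says which one settles the trial.

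Three further weaknesses follow from the stated methods:

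- None of the four tests has baseline EAT-26 as a covariate. The group-by-time term uses baseline only through differencing, as a change score does.
- The rank versions give no mean difference to set against the 20 points in the sample size section. The reported effect measure would therefore depend on how a normality test falls in about 40 patients.
- McNemar's test is a paired, within-patient test. It cannot compare arms, although the sentence offers it for comparing groups. This does not touch the primary outcome, which is a total score.

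At stake are the clarity of the primary result and, with about 20 evaluable patients per arm, some precision that the collected data could supply.

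**Working it through.** **Inputs from the article.** 40 evaluable patients from 50 randomised, 20% dropout, equal allocation, a 20-point difference, 80% power.

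**Assumptions (not given in the article).** Two-sided 5% level; the 20 points read as a between-arm difference; equal SD s at each visit; V1-V2 correlation r varied from 0 to 0.7.

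**Step 1: the plan's own figure.** 40 / (1 − 0.20) = 50, so the dropout step reproduces. The 40 cannot be checked because no SD is given. Solving backwards with 20 per arm: s = 20 / [√(2/20) × (1.960 + 0.842)] = 20 / 0.886 = 22.6.

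**Step 2: precision of each analysis.** The per-patient variance is:

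- V2-only ANOVA: s²
- change score (the same test as a two-visit group-by-time term): 2s²(1 − r)
- ANCOVA: s²(1 − r²)

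The ratio of ANCOVA to change score is (1 − r²) / [2(1 − r)] = (1 + r)/2. The ratio of ANCOVA to V2-only is 1 − r². Neither exceeds 1, so under approximate normality ANCOVA is asymptotically never less precise than either.

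**Step 3: analytic power, 20 per arm, s = 22.6, difference 20.**

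| r | V2-only | Change | ANCOVA |
|---|---|---|---|
| 0 | 0.80 | 0.508 | 0.80 |
| 0.3 | 0.80 | 0.658 | 0.836 |
| 0.5 | 0.80 | 0.80 | 0.899 |
| 0.7 | 0.80 | 0.951 | 0.975 |

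At r = 0.5 the change score has 80% power. For ANCOVA the standardised effect is 2.802 / √0.75 = 3.235; 3.235 − 1.960 = 1.275, which gives 0.899. A simulation with the effect set so that the change score has 80% power gave 89%.

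**Step 4: simulated power (3,000 trials per setting, effect held to V3).**

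| Data | Analysis | r = 0.3 | r = 0.5 | r = 0.7 |
|---|---|---|---|---|
| Normal | ANCOVA | 0.813 | 0.876 | 0.963 |
| Normal | V2-only ANOVA | 0.779 | 0.782 | 0.788 |
| Normal | Change score | 0.638 | 0.785 | 0.946 |
| Normal | Three-visit interaction | 0.677 | 0.822 | 0.970 |
| Strongly skewed | ANCOVA | 0.791 | 0.866 | 0.942 |
| Strongly skewed | V2, Shapiro-Wilk gated | 0.922 | 0.921 | 0.925 |
| Strongly skewed | Change, Shapiro-Wilk gated | 0.725 | 0.868 | 0.967 |

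**Step 5: simulated type I error (6,000 trials per setting, normal and skewed data, r = 0.3 to 0.7, nominal 0.05).**

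- Any one fixed test other than ANCOVA: 0.042 to 0.055
- Shapiro-Wilk gate followed as written, within one route: 0.048 to 0.057
- ANCOVA alone: 0.045 to 0.053
- Success on any of gated V2, gated change or the three-visit interaction, uncorrected: 0.113 to 0.125

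The aligned rank-transform version was not simulated.

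**Step 6: what a three-visit test asks.** With equal correlations, its power depends on the squared spread of the between-arm differences over the visits. For differences (0, d, d) that is (4 + 1 + 1)d²/9 = 2d²/3. For (0, d, 0) it is also 2d²/3. For (0, d, d/2) it is d²/2. For (0, 0, d), with no effect at V2 at all, it is again 2d²/3. If V3 is included, the test is therefore not a test of the V1-to-V2 change.

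**The case against.** The strongest reply has five parts.

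1. The choice between parametric and rank tests is not made at will. The rule is stated in advance and, followed literally, leaves the error rate near 5%. This stands. A reader might infer that the normality gate itself inflates the error rate, and step 5 does not support that.
2. The 11 to 12% needs success on any of several tests without correction. The article never says this, and it names Bonferroni and ICH E9. This stands too. Bonferroni over those three tests (0.05/3 each) would bring the total back to about 5%. What remains is that the family is undefined, so the sentence neither identifies the deciding test nor guarantees that correction.
3. The endpoint is a change, so it fits the across-visits sentence. That sentence may mean baseline to endpoint and baseline to follow-up taken separately, in which case the first comparison is exactly the change-score test. This reading is fair. For the same reason, the claim that patients without V3 would be dropped is only an inference: it needs the three-visit reading, and the article states no deletion rule. Yet the between-group sentence also covers quantitative outcomes, so the text does not settle which route applies.
4. A change score is a valid analysis of a change, and covariates are often left to an analysis plan. Agreed: the point is not that detail is missing. The article does state its methods, and a better one is available from data already collected.
5. ANCOVA is not always more powerful. This stands, as step 4 shows.

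**Conclusion.** The point holds as a correction to stated methods, not as evidence that the trial's error rate is wrong. The article ties no one test to the V1-to-V2 EAT-26 endpoint, lets a normality test decide whether a mean difference is reported, and makes no covariate use of baseline.

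The 11 to 12% type I error is a worst case under an uncorrected any-of-several rule. It should not be read as the error rate of the plan as written.

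The gain from ANCOVA is real under approximate normality, but its size rests on assumptions because no SD, correlation or distribution is given. At an assumed r = 0.5 it is about 80% to 89 or 90% against the change score. It is nil against V2-only ANOVA at r = 0. At r = 0.7, ANCOVA and the three-visit analysis are about equal if the effect persists to V3 (0.963 against 0.970). With strongly skewed scores a rank test can do better. A reader might call the present options wholly unadjusted or generally wasteful; neither holds, since the group-by-time term does use baseline, as a change score.

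**What to change.** In the Statistical methods section:

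- Name one primary analysis: ANCOVA of V2 EAT-26 on arm with V1 EAT-26 as covariate, two-sided 5%, reporting the adjusted mean difference with its 95% confidence interval.
- Keep a rank-based analysis as a sensitivity analysis, so that the Shapiro-Wilk result no longer selects the primary test.
- Report the V3 comparison as a separate secondary contrast.
- For any binary comparison of arms, replace McNemar's test with a between-arm test.

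ANCOVA does not by itself deal with patients who lack a V2 score. With 20% dropout expected, their handling should be stated wherever the full analysis plan sets it out.

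The cost is wording only. EAT-26 is already collected at V1, V2 and V3, and neither the visits nor the sample size changes.

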### Eligibility criteria

A total of 50 inpatients (before accounting for a 20% dropout) with a diagnosis of anorexia nervosa (AN) will be recruited for this study. To be eligible for the trial, subjects must fulfill all of the inclusion criteria and none of the exclusion criteria, as stated below. The following inclusion criteria will be adopted:

Written informed consent to participate in this study before any study-mandated procedure, written by the participant or participant and parent/legal guardian;Female patients aged 13–25 years old;Meet the DSM-5 criteria for AN;Body mass index (BMI)  ≤ 17,5 kg/m2;Participants must not be undergoing psychopharmacotherapy, with the exception of those who have been taking antidepressants for a minimum of 1 month in a stable dose.

The exclusion criteria will be as follows:

No informed consent to participate in the study;Diagnosis of neurological/organic diseases, such as epilepsy;Contraindications to tDCS, ie., pacemakers, metal parts around the head;Any psychiatric comorbidities;Pregnancy or pregnancy planning;Taking medications other than antidepressants or changes in psychopharmacotherapy during the study.

Reasons for the participant to be discontinued from the study:

Withdrawal of informed consent,.Completion of hospitalization before the end of participation in the project.Non-attendance at the study visits and stimulations understood as equal to or greater than 10% of all simulations.Any serious adverse event during the intervention period.

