### Interventions

Patients will be receiving twice a day tDCS (applied current at 2mA) or sham stimulation, for 3 weeks on working days (30 sessions in total). Each stimulation will last 25 minutes and take place at a two-hour interval. The detailed schedule of meetings and measurement methods is presented in **Table 1**.

**Table 1 T1:** Schedule of enrolment, interventions, and assessments.

	Study Period				
	Enrolment	Baseline	Intervention period (tDCS stimulations)	End of the intervention period	Safety Follow-up
Timepoint (day)	-2 to -1	0	1-21 ( ± 1 days)	22 ( ± 1 days)	35 ( ± 7 days)
Visit number	V0	V1		V2	V3
Eligibility screen	X				
Informed consent	X				
Sociodemographic data	X				
Randomization		X			
ASSESSMENTS:					
Weight	X	X	X	X	X
Performing body composition analysis		X		X	X
Psychological		X		X	
Neuropsychological		X		X	
Dietary behaviors and nutrition		X		X	X
Biological	X	X	X	X	
Adverse events	X	X	X	X	X

Participants in the active tDCS group will receive active stimulation to DLPFC via two saline-soaked, 25 cm2 (5 cm x 5 cm) sponges saline-soaked placed over F3 (anode) and F4 (cathode), according to the International 10–20 system. The electrodes will be placed on the patient’s head using a specially designed headband. The patient’s skin should be clean and dry. Each time, it will be checked whether the skin has any wounds, irritations, or other dermatological issues that could affect the safety and comfort of the patient.

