## Data collection methods

To evaluate the efficacy of the intervention on the symptoms of patients with AN, the following changes will be determined:

1. Using paper-pencil questionnaires:

a) the severity of depression symptoms between V1 and V2 measurement (BDI total score/CDI2 total score);

b) the severity of symptoms of eating disorders and inappropriate eating behaviors (EAT-26 total score, QEB total score, EDE-Q 6.0 total score, FIVq total score);

c) neurocognitive functions between V1 and V2 measurement (total score: APT, ROCF, CTT-1, CTT-2, BVMT, VFT).

d) psychological measurements connected with dysfunctional metacognitive beliefs, other aspects related to thinking (such as reflectivity, impulsivity, rumination) and obsessive-compulsive symptoms, stress levels and assessment of early childhood injuries related to the experience of abuse, emotional, bodily, sexual, emotional, and physical neglect, and self-assessment of the appearance of one’s body between V1 and V2 measurement (total score: MCQ-A, RRQ, MTT, CY-BOCS, PSS-10; CTQ, ASRS),.

2. To evaluate the effect of the intervention on physiological parameters, the following changes will be measured:

a) In serum, from the baseline (V1) to the end of the stimulation (V2), levels of:

CBC, ferritin, TSH, FT3, FT4, electrolytes: phosphorus, magnesium and calcium, HPA axis biomarker: cortisol, markers of food intake regulation (plasma leptin and serum visfatin), neurotrophins (serum brain-derived neurotrophic factor: BDNF, nerve growth factor: NGF, neurotrophin 3 and 4.

Blood will be drawn by a qualified hospital staff member, and then a portion of it will be analyzed in the hospital laboratory, while another part will be frozen for conducting ELISA analyses at the level of neurotrophins, cortisol, and food intake regulators after the completion of the group collection.

b) Anthropometric data, from the baseline (V1) to the end of the study (V3):

Body weight will be measured, and body composition will be analyzed using the electrical bioimpedance method (BIA), Impedimed SFB7 BIS Research Device will be used. Anthropometric measurements will be carried out by a dietitian.

c) Brain activity, at the baseline (V1) and at the end of the stimulation (V2): EEG. The examination and analysis will be conducted by a qualified employee of the clinical neuropsychology laboratory.

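### Weight is scheduled at five points, but the planned ANOVA for weight/BMI uses three visits and drops incomplete patients; a mixed model on all recorded weights would keep them at little cost

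*Protocol article*

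**What the plan says.** Table 1 of the protocol article ("Schedule of enrolment, interventions, and assessments") marks weight in all five columns: enrolment (V0), baseline (V1), the intervention period (days 1 to 21), end of intervention (V2) and follow-up (V3). It does not say how often patients are weighed during stimulation.

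The Statistical methods section has one general sentence for all outcomes: "To compare groups between baseline and endpoint assessments and follow-up assessments, repeated measures of ANOVA", with an aligned-rank version as the alternative. It names no other time points. For dropouts it plans only a descriptive comparison with the remaining participants.

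Secondary outcomes are "defined as changes in: 1. anthropometric measurements (in this BMI), 2. brain bioelectric activity" and so on, so BMI sits in the first-listed item. The same section places BMI at V1 and V2, "with additional measurements of BMI and BIA analysis also at V3". Data collection methods defines anthropometric change from V1 to V3.

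The Sample size calculation allows for 20% dropout: 50 enrolled, 40 evaluable. Among the reasons for discontinuation, Eligibility criteria lists "Completion of hospitalization before the end of participation in the project".

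**The concern.** A conventional repeated-measures ANOVA needs a value at every included visit. A patient who leaves hospital in week 2 has no V2 or V3 and falls out of the weight/BMI comparison, although her V0, V1 and in-treatment weights have been recorded. Those weights carry information about where she was heading, and the plan gives them no part in the analysis.

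Two things are at stake. The first is precision on BMI: nutritional rehabilitation is part of the trial's stated main purpose, and the sample is small. The second is bias: if leaving depends on weight already gained, the patients who remain are a selected group, and the earlier weights are what a model would need to allow for that.

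**Working it through.** **1. Schedule against analysis.**

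| | V0 | V1 | During stimulation | V2 | V3 |
|---|---|---|---|---|---|
| Weight scheduled (Table 1) | yes | yes | yes | yes | yes |
| Named in the ANOVA sentence | no | yes | no | yes | yes |
| Stated as a BMI outcome visit | no | yes | no | yes | yes |

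**2. The plan's own figure.** 40 / (1 − 0.20) = 50, as stated. With equal allocation this is 25 randomised and 20 evaluable per arm. The 20% was set for EAT-26; I assume that it applies to weight too.

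**3. Cost of losing cases.** The variance of an arm difference is proportional to 1/n, so recovering all the lost cases would give a ratio of at most 25/20 = 1.25. The corresponding cut in standard error is at most 1 − √(20/25) = 10.6%.

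**4. How much can be recovered.** The inputs are assumptions, because the documents give none:
- weekly weighing, with V0 1.4 days before V1 (Study timeline says 1 to 2 days);
- patient intercept SD 5 kg, slope SD 0.35 to 0.5 kg/week, day-to-day SD 0.4 to 1.0 kg;
- 5 of 25 per arm lost, half after week 1 and half after week 2 on average.

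Complete-case V1-to-V2 change, 20 per arm, 3 weeks: Var = (2/20) × (3² × slope SD² + 2 × day-to-day SD²). For SDs of 0.35 and 0.7: 0.1 × (9 × 0.1225 + 2 × 0.49) = 0.1 × 2.0825 = 0.208.

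Mixed model with known covariance, common pre-treatment mean and free means by week and arm: Var = c′(Σ nₚ Xₚ′ Σₚ⁻¹ Xₚ)⁻¹c, summed over dropout patterns p and both arms.

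| Slope SD | Day-to-day SD | Complete-case variance | Mixed model, V1–V3 | Ratio | Mixed model, V0–V3 | Ratio |
|---|---|---|---|---|---|---|
| 0.35 | 0.4 | 0.1422 | 0.1253 | 1.135 | 0.1232 | 1.155 |
| 0.35 | 0.7 | 0.2082 | 0.1893 | 1.100 | 0.1757 | 1.185 |
| 0.35 | 1.0 | 0.3103 | 0.2840 | 1.092 | 0.2514 | 1.234 |
| 0.50 | 0.4 | 0.2570 | 0.2205 | 1.165 | 0.2194 | 1.171 |
| 0.50 | 1.0 | 0.4250 | 0.3848 | 1.104 | 0.3580 | 1.187 |

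The ratio is about 1.09 to 1.17 without V0 and 1.16 to 1.23 with it. Taken together this is roughly 1.1 to 1.25. Since √1.1 = 1.049 and √1.25 = 1.118, the complete-case standard error is about 5% to 12% larger. The ratio reaches 1.19 to 1.36 only if linear gain is imposed.

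**5. With complete follow-up.** With free visit means, adding weekly in-treatment weights to V1, V2 and V3 leaves the variance of the V2 contrast unchanged. The ratio was 1.000 under compound symmetry, AR(1) and random-slope covariances.

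**6. The in-treatment weights alone.** The comparison here is a likelihood model on V1, V2 and V3 that already keeps the dropouts' baselines. Adding the in-treatment weights at 20% loss cuts the standard error by about 1% to 7% across those covariances. The gain in step 4 is therefore partly from these weights and partly from V0 acting as a second baseline reading.

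**The case against.** The strongest reply is that BMI is defined at V1, V2 and V3 and the analysis uses exactly those visits. In-treatment weight is never named as an outcome and may be ward monitoring. Table 1 also marks biological tests at V0 and during the intervention, yet biological outcomes are defined at V1 and V2 only, so a mark in that column does not make a measurement an efficacy measurement. The ANOVA sentence is general, and model detail for one secondary outcome often sits in an analysis plan that is not shown. This stands against calling the plan wrong. It does not answer the point that the stated method loses incomplete patients whose weights exist.

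A reader might infer three stronger things that the documents do not support.

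- **That the trial throws the weights away.** No section says so; the article is silent on their use.
- **That a large loss of precision or power follows.** Simulated variance ratios of 1.40 to 1.59, and power of 60% against 80%, can be produced, but only by adding a further 15% of patients without V3 to the 20% dropout. That leaves 0.80 × 0.85 × 50 = 34 patients, against the plan's 40. It also assumes that a missing V3 removes a patient from the V1-to-V2 comparison, which the plan does not state.
- **That the planned estimate is biased towards no effect.** Simulations show this if patients leave once recorded gain passes 3 to 4 kg. No such trigger, weight effect or link between discharge and weight appears in the documents, and those simulations generate data that suit the mixed model. Weight-related leaving is plausible, but no size can be given. The planned comparison of dropouts would describe such selection without correcting it.

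**Conclusion.** The concern holds in a modest form. The plan names a complete-case method over three visits for weight/BMI, expects to lose 20% of patients, and gives no stated role to other weights that it schedules. A mixed model on all recorded weights is better suited to these data.

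The complete-case variance is roughly 1.1 to 1.25 times the mixed model's at 20% loss. This rests on weekly weighing and on the assumed variance components and dropout timing. Treating the components as known slightly flatters the mixed model. If nearly everyone reaches V2, the in-treatment weights gain almost nothing for that contrast. Bias is reduced only if leaving depends on weights already recorded.

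The primary analysis of EAT-26 is unaffected. This is a worthwhile, inexpensive improvement to a secondary outcome.

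**What to change.** In Statistical methods, for weight and BMI only, replace the three-visit ANOVA with a likelihood-based linear mixed model that:

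- uses all recorded weights from V0 to V3, with actual measurement dates, for all randomised patients;
- has a common pre-treatment mean across arms, time as visit or week categories, and arm-by-time terms;
- reports the arm differences at V2 and V3 with 95% CIs.

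Keep a piecewise-linear random-slope model, with a change of slope at the end of stimulation, as a sensitivity analysis. State how often weight is recorded during stimulation. Fix the change before unblinding, so that the choice of model cannot look data-driven.

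The cost is a few lines of text and some extra analysis, with no new data or patients. The downside is the assumption that data are missing at random given recorded weights. The recorded data cannot prove it, so the planned comparison of dropouts with completers should be kept and reported alongside.

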### Allocation

The patients included in the study will be randomly assigned to one of two subgroups, independently of examined variables, during the entry of the study: Active group - AG (tDCS group, n=25) and Sham group - SG (placebo group, n=25).

Eligible patients will be randomized in equal proportions between the AG and SG arm. A random sequence generator (Urbaniak GC, Plous S. Research Randomizer (Version 4.0) 2013) will be used to randomize active versus sham arms. The allocation to study groups will be performed by a researcher not involved in the stimulation and assessment of patients.

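### Bonferroni is a valid choice here, but Holm's step-down rule gives the same familywise protection and never rejects less: a one-sentence improvement with a modest gain

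*Protocol article*

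**What the plan says.** The protocol article, under Statistical methods, names one multiplicity rule: "Bonferroni correction of obtained significance levels will be used to correct for multiple comparisons". It names no step-down variant, so the ordinary single-step meaning is the natural reading. The sentence does not say which comparisons form the family. It follows the sentence on repeated-measures analyses and does not mention the secondary outcomes. It adjusts significance levels only, and the section mentions no confidence intervals.

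Under Secondary outcome measures, "a range of secondary outcome measures will also be utilized, defined as changes in" introduces seven domains. Power is planned for the primary outcome alone: "The statistical power was estimated at 80% to detect a difference in means of EAT-26". The target number is given as "To account for a dropout rate of 20%, a total of 50 individuals will be included to achieve a target number of 40 participants", and Allocation states "Eligible patients will be randomized in equal proportions between the AG and SG arm".

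**The concern.** Bonferroni compares every p-value in a family of m tests with 0.05/m. Holm orders the p-values and compares them in turn with 0.05/m, 0.05/(m−1), and so on up to 0.05, stopping at the first failure. Both hold the familywise error at 5% without any assumption about how the tests are related. Because Holm can only add rejections, fixing Bonferroni gives up some power with no gain in error control.

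The trial is small and measures many things, so it is worth asking how much power is given up. Neither the primary analysis nor the validity of the adjusted tests is at stake.

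**Working it through.** **Inputs from the article.** The dropout step reproduces: 40/(1 − 0.20) = 50. With 1:1 allocation, 40/2 = 20 evaluable patients per arm. The article gives no figure for the multiplicity procedure itself, so there is nothing further of its own to reproduce.

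**Assumed inputs.**
- Alpha is 0.05 two-sided, because the article states none.
- Family size is m = 7 (one test per listed domain) or m = 35. The second is a count from Data collection methods without EAT-26: 1 depression score + 3 other dietary questionnaires + 6 neurocognitive + 7 psychological + 15 blood markers + 2 anthropometric + 1 EEG = 35. Blood count, body composition and EEG each count as one.
- The standardised difference d is 0.5, 0.8, 0.9 or 1.2. For orientation, 80% power at 20 per arm needs d of about 0.91. For the 20-point EAT-26 improvement that implies an SD of about 20/0.91 = 22, which the article does not state.
- Correlation between tests is 0 or 0.5.

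**Step 1: Holm never rejects less.** For m = 7, Bonferroni uses 0.05/7 = 0.0071 throughout. Holm uses 0.0071, 0.0083, 0.0100, 0.0125, 0.0167, 0.0250 and 0.0500. No Holm threshold is below 0.05/m, so every Bonferroni rejection is also a Holm rejection.

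**Step 2: Holm keeps the same error rate.** Suppose m₀ of the m null hypotheses are true. When Holm first rejects a true null, at most m − m₀ hypotheses have gone before it, so the threshold in use is at most 0.05/m₀. By the union bound the chance of this is at most m₀ × 0.05/m₀ = 0.05, under any dependence.

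**Step 3: Bonferroni power.** With 20 per arm, a two-sample t-test has 38 degrees of freedom and noncentrality d√(20/2). At d = 0.9 this is 2.85. Tested at 0.05/7 the power is about 51%, and at 0.05/35 about 30%.

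**Step 4: size of the gain.** The table gives average power per true effect, Bonferroni → Holm, in %, from two-sided t-tests with correlation 0.5 and 20,000 replicates per cell:

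| m | real effects | d = 0.5 | d = 0.8 | d = 1.2 |
|---|---|---|---|---|
| 7 | 1 | 11.9 → 12.0 | 38.8 → 38.9 | 82.3 → 82.4 |
| 7 | 4 | 11.7 → 12.7 | 38.9 → 42.2 | 82.1 → 85.7 |
| 7 | 7 | 12.0 → 14.4 | 39.0 → 48.8 | 82.1 → 91.6 |
| 35 | 7 | 4.4 → 4.5 | 20.2 → 20.7 | 63.7 → 65.0 |
| 35 | 18 | 4.3 → 4.6 | 20.4 → 22.1 | 63.5 → 68.1 |
| 35 | 35 | 4.3 → 5.0 | 20.4 → 25.8 | 63.9 → 79.0 |

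Further runs at d = 0.9 agree. With m = 7, power goes from 51.2% to 51.3% with one real effect, from 50.5% to 52.9% with three, and from 50.8% to 62.0% with all seven. With m = 35 and seven real effects it goes from 29.7% to 30.5%.

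Uncorrelated tests give similar gains. The largest there are 4.2 points (m = 7, four real), 5.1 (m = 35, eighteen real), 11.8 (m = 7, all real) and 18.5 (m = 35, all real), each at d = 1.2.

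**Step 5: at least one true rejection.** This probability changed by less than 0.2 points in every setting. Holm's first threshold is Bonferroni's threshold, so Holm can add a first true rejection only after a false one has opened the way.

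**Step 6: error rate as simulated.** Both rules stayed at about 0.05 or below. The highest estimate, 0.052, came from seven independent tests with no real effect. There the exact value is 1 − (1 − 0.05/7)⁷ = 0.049, so the excess is simulation noise.

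**The case against.** The strongest reply is that nothing here is an error. Bonferroni is standard, valid under any dependence and conservative. No secondary outcome has a power target, so no stated figure is missed. Bonferroni also has simple simultaneous intervals that match its tests, which Holm lacks. All of this stands, though the article's sentence adjusts only significance levels and no intervals are planned in that section.

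A reader might go further in three ways that the document does not support.

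- **That power on the secondary outcomes is thrown away for nothing.** The sentence names no family and could equally concern contrasts between visits or groups within one outcome. The link to the secondary outcomes is an inference, and the family definition may sit in an analysis plan that is not shown. The interval property also means that Bonferroni is not without compensation.
- **That true effects will be reported as non-significant because of this choice.** That happens to a material degree only if several effects are real and large.
- **That the chance of confirming all seven domains roughly triples.** It does rise from about 12% to 38% in one setting, but that setting needs one test per domain and all seven effects real at d = 0.9. The Introduction reports that the only earlier double-blind randomised trial found no significant improvement in psychopathology or weight over sham. The Discussion cites studies in which stimulation left cortisol unchanged. The list of measures in which change is to be assessed also includes a retrospective childhood-trauma questionnaire. This setting is therefore not a fair headline.

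**Conclusion.** The point stands as a cheap improvement and not as a defect. Holm is at least as powerful as Bonferroni for any family of comparisons, with identical familywise control, and that conclusion needs no assumption about effects or correlation.

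The size of the gain does rest on assumptions: 20 evaluable per arm, two-sided 5%, 7 or 35 tests, d from 0.5 to 1.2, and correlation 0 or 0.5. Under these it is roughly 0 to 3 points of average power per true effect in most scenarios. It reaches 4 to 5 points if about half the effects are real and very large (d = 1.2). With seven tests it is about 12 points only if all seven effects are real and large; the 15 to 19 points seen with 35 tests require all 35 to be real at d = 1.2. The chance of finding at least one true effect hardly moves.

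**What to change.** Replace the Bonferroni sentence in Statistical methods with:

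> Within each family of comparisons to which a multiplicity correction applies, p-values will be adjusted by the Holm step-down procedure (familywise 5%, two-sided).

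This wording leaves the choice of families where the trial team has placed it. The adjusted p-values come from the ordered raw ones: the j-th smallest becomes the largest, over i ≤ j, of min{1, (m − i + 1)·p₍ᵢ₎}. No new data or change to design or sample size is needed, and a permutation method is unnecessary.

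The one cost concerns intervals. Any confidence intervals shown beside Holm-adjusted p-values should be labelled as unadjusted, because such an interval can exclude zero while the adjusted test does not reject.
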